### Statistical analysis

#### Sample size

The required sample size was based on the following considerations. We assume a delay of PMFS after MDT alone of approximately 21 months [9]. We consider an additional median delay of PMFS of 12 months in arm B and another additional 12 months of PMFS in Arm C as clinically meaningful. The sample size calculation was determined for a two-sided long-rank test for each of the three pairwise comparisons (Arm A vs. Arm B, Arm A vs. Arm C, Arm B vs. Arm C). We suppose a 5-years of accrual and a minimum of 5 years of follow-up to determine the primary endpoint with a 10% 5-year censoring (drop-out) rate. To account for multiple testing, a Bonferroni-correction was applied, implying a test-wise significance level of 0.0167, in order to keep a family-wise significance level of 5%. A sample size of 873 patients is required (291 patients in each arm) to obtain a power of at least 80% in each of the three tests.

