#### Data analysis

Patients will be analysed in the groups to which they are assigned (intention-to-treat). A stratified two-sided log-rank test will be used for the three pairwise comparisons of the primary analysis, to test for a difference between the three treatment arms with regards to poly-metastasis free survival (PMFS). A Bonferroni correction will be applied to guarantee a study-wise 5% significance level for the primary endpoint. Stratification factors are PSA doubling time (≤ 3 vs. > 3 months), number of metastases (1 versus > 1) and initial localization of metastases (M1a vs. M1b and/or M1c). Kaplan–Meier estimates will be obtained, and a KM curve will be constructed. The hazard ratio (HR) will be determined with 95% confidence interval by means of a Cox proportional hazards model. For the evaluation of mCRPC-FS, cPFS and OS the same method will be used as for the primary endpoint. CSS will be estimated using the cumulative incidence function rather than the Kaplan–Meier estimates to count for death of other causes as a competing event.

Group differences with regards to longitudinally measured ordinal outcomes such as toxicity will be analysed by means of proportional odds models with estimation based on generalized estimating equations (GEE). Multiple imputation will be applied in case of considerable drop-out, providing consistent estimates under a missing-at-random (MAR) drop-out pattern, hence when the probability of drop-out depends on treatment group or previous observations. Group differences with regards to longitudinally measured continuous outcomes such as quality of life scores will be analysed by means of linear mixed models. Likelihood methods will then be used for parameter estimation providing valid inference under MAR. For all longitudinal analyses, the explanatory model will contain both treatment group, time point of measurement and their interaction in order to test post-hoc group effects at specific time points. Statistical analysis will be performed using SAS software.

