#### Interim analysis

An interim analysis is planned approximately after 60 months and after including 179 patients in each arm. A that time we have at least 80% power to analyse arm A vs. arm B and arm A vs. arm C. To control the type I error, both tests will be evaluated at a significance level of 0.0083. If both tests are significant, arm A can be stopped. Otherwise, all arms will be continued. In such case, the final analysis will compare arms B and C at a significance level of 0.0167. In case of significance of either arm B or C versus arm A at interim analysis, the final analysis of the remaining comparisons will also be performed at a significance level of 0.0167. In case both comparisons at the interim analysis are non-significant, both arm B and C will be compared with arm A at the final analysis at a significance level of 0.0083.

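### B vs C is held at 0.0167 on every path, although 5% family-wise control allows 0.05 once any comparison is rejected; its power would rise from about 80% to 90% at the same sample size

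*Protocol article*

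**What the plan says.** The Sample size section of the protocol article plans a two-sided log-rank test for each of A vs B, A vs C and B vs C, and fixes the level: "To account for multiple testing, a Bonferroni-correction was applied, implying a test-wise significance level of 0.0167". The 291 patients per arm (873 in total) are sized on that level, for at least 80% power in each test. The Data analysis section repeats the approach: "A Bonferroni correction will be applied to guarantee a study-wise 5% significance level for the primary endpoint".

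The Interim analysis section tests A vs B and A vs C at 0.0083 each, at about month 60. Its rules for the final analysis are:

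- Both significant at the interim: arm A can be stopped, and "the final analysis will compare arms B and C at a significance level of 0.0167".
- One significant: the remaining comparisons are tested at 0.0167.
- Neither significant: A vs B and A vs C are tested at 0.0083.

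No path gives B vs C a level above 0.0167, and no step-down or closed procedure is described.

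**The concern.** The three null hypotheses (A=B, A=C, B=C) are not free of one another, because any two of them imply the third. Once one is false, at most one other can be true, so at most one false positive remains possible. Dividing 5% by three at that stage corrects for a multiplicity that no longer exists. The clearest case is the one the Interim analysis section describes: both comparisons with A are already rejected, B vs C is the only primary hypothesis left, and it is still tested at a third of 5%.

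The loss falls on the comparison least able to bear it. B vs C has the smallest planned effect, is the only comparison near 80% power, and determines the size of the trial.

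**Working it through.** **Inputs (Sample size section).** Median PMFS is 21 months in A, 21 + 12 = 33 in B and 33 + 12 = 45 in C. Accrual takes 60 months, follow-up is at least 60 months, and drop-out is 10% at 5 years. Assumptions added here: exponential survival and drop-out, uniform accrual.

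**Hazard ratios.** A/B 21/33 = 0.636; A/C 21/45 = 0.467; B/C 33/45 = 0.733.

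**Reproducing the plan's sample size (B vs C).**

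- Events (Schoenfeld): 4(z₁₋α/₂ + z₀.₈)² / (ln HR)² = 4(2.394 + 0.842)² / 0.310² ≈ 435.
- Event probability per arm: λ/(λ+γ) × [1 − (e^(−60(λ+γ)) − e^(−120(λ+γ))) / (60(λ+γ))], with λ = ln 2/median and γ = −ln(0.9)/60. This gives 0.794 in B and 0.697 in C, mean 0.746.
- Patients per arm: 435/(2 × 0.746) ≈ 292, or 293 with events rounded up, against 291 stated. The plan is reproduced.
- The same method needs about 121 per arm for A vs B and 46 for A vs C, so B vs C alone sets the size.

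**Power of B vs C at 291 per arm.** Expected events are 582 × 0.746 ≈ 434, and the drift is √434/2 × 0.310 ≈ 3.231.

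| Level | Power | Events for 80% power |
|---|---|---|
| 0.0167 | Φ(3.231 − 2.394) = 79.9% | 435 |
| 0.05 | Φ(3.231 − 1.960) = 89.8% | 326 |

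At 0.0167, A vs B has 99.6% power and A vs C about 100%.

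**Why 0.05 is allowed.** In a closed test, the intersection of any two pairwise nulls is the global null A=B=C. The plan's first-rejection levels already test it within 5%: A vs B and A vs C at 0.0083 at each of two looks, and B vs C at 0.0167 once, so 4 × 0.0083 + 0.0167 = 0.05. After the global null is rejected, each single null needs only its own 5% test. B vs C has no interim look, so its full 0.05 is available at the final analysis. A vs B and A vs C have 0.05 − 0.0083 = 0.0417 left.

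**Simulation under the planned medians.**

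| Setting | B vs C, plan | B vs C, closed |
|---|---|---|
| No interim, 10,000 trials | 80.0% | 89.5% |
| Interim at month 60, 291 per arm, 2,000 trials | 80.2% | 90.3% |
| Same, separate run, 4,000 trials | 79% | 89% |
| Interim with 179 per arm by month 60, two runs | 81% and 83% | 90% and 91% |

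In the 2,000-trial run, all three comparisons were significant in 79.9% of trials under the plan and 90.1% under the closed test. Without the interim, a first rejection occurred in all 10,000 trials, and every Bonferroni rejection was kept.

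**Family-wise error of the closed test.**

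- No interim: 4.6% with all arms equal (the same as Bonferroni) and 5.0–5.1% with one pair equal (Bonferroni 1.7–1.8%).
- With the interim, 2,000 trials per scenario: 0.043 with all arms equal and 0.038–0.051 with one true null (simulation error 0.005). The plan's rule gave 0.015–0.024 with one true null.
- With the interim, 4,000 trials per scenario: 4.3–5.3%.

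**If the planned effects are wrong.** With medians 33/33/45 (no interim), a first rejection occurs in 92% of trials and B vs C power goes from 79.6% to 86.6%. With a 42-month median in C, B vs C power by formula is 55% at 0.0167 and 72% at 0.05.

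**The case against.** The plan is not in error. It controls family-wise error and delivers about the 80% power it promises, so one can call this optimisation. That is fair as a description: the point concerns avoidable loss, not inflated error. But the present rule is beaten by another that can be prespecified at the same sample size and never loses a rejection, and the loss falls on the comparison that sets the sample size.

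The plan already recycles some alpha: after one interim rejection, the other comparison with A moves from 0.0083 to 0.0167. That is true, but B vs C gains nothing from it.

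The added rejections are modest observed effects. With 434 events, the critical hazard ratio moves from about 0.795 to 0.828. Against a 33-month median in B, that is an observed gain of about 8.5 and 6.8 months, both below the 12 months called clinically meaningful. A sponsor may deliberately want a stricter bar for C over B. That would be a legitimate reason, but the article does not give it: it gives 0.0167 purely as a multiplicity correction. The present bar also admits observed gains below 12 months.

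Two limits stand. The higher level is available only after a first rejection, which is near certain only if the planned effects are about right. And simultaneous confidence intervals matching a step-wise test are less simple. The Data analysis section plans ordinary 95% intervals for the hazard ratio, which do not match tests at 0.0167 either.

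**Conclusion.** The concern holds. The plan tests B vs C at a third of the level that 5% family-wise control permits once any other comparison is rejected. Under the planned effects this costs about 10 percentage points of power (79.9% against 89.8%), roughly half of the false-negative risk in that comparison. The simulated gain was about 8 to 10 points, depending on accrual by the interim. The figures assume exponential survival and uniform accrual, which reproduce the stated sample size to within 1%. The error control follows from the closure principle and does not depend on those assumptions. This is a worthwhile improvement to a valid plan, not a correction of a false one.

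**What to change.** Amend the Sample size, Data analysis and Interim analysis sections to prespecify a closed (Shaffer-type) procedure:

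1. For the first rejection, keep the present levels: A vs B and A vs C at 0.0083 at the interim and 0.0083 at the final analysis, B vs C at 0.0167 at the final analysis (total 0.05).
2. Once any comparison is rejected, test B vs C at 0.05 at the final analysis, and each remaining comparison with A at 0.05 in total (0.0083 at the interim, 0.0417 at the final analysis).
3. State which confidence intervals accompany the step-wise tests.

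If a stricter bar for C over B is intended, say so and give the reason.

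The cost is a few sentences and less simple simultaneous intervals. Sample size, treatment and visits are unchanged. The rule must be fixed before the interim comparison is seen.

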#### Data analysis

Patients will be analysed in the groups to which they are assigned (intention-to-treat). A stratified two-sided log-rank test will be used for the three pairwise comparisons of the primary analysis, to test for a difference between the three treatment arms with regards to poly-metastasis free survival (PMFS). A Bonferroni correction will be applied to guarantee a study-wise 5% significance level for the primary endpoint. Stratification factors are PSA doubling time (≤ 3 vs. > 3 months), number of metastases (1 versus > 1) and initial localization of metastases (M1a vs. M1b and/or M1c). Kaplan–Meier estimates will be obtained, and a KM curve will be constructed. The hazard ratio (HR) will be determined with 95% confidence interval by means of a Cox proportional hazards model. For the evaluation of mCRPC-FS, cPFS and OS the same method will be used as for the primary endpoint. CSS will be estimated using the cumulative incidence function rather than the Kaplan–Meier estimates to count for death of other causes as a competing event.

Group differences with regards to longitudinally measured ordinal outcomes such as toxicity will be analysed by means of proportional odds models with estimation based on generalized estimating equations (GEE). Multiple imputation will be applied in case of considerable drop-out, providing consistent estimates under a missing-at-random (MAR) drop-out pattern, hence when the probability of drop-out depends on treatment group or previous observations. Group differences with regards to longitudinally measured continuous outcomes such as quality of life scores will be analysed by means of linear mixed models. Likelihood methods will then be used for parameter estimation providing valid inference under MAR. For all longitudinal analyses, the explanatory model will contain both treatment group, time point of measurement and their interaction in order to test post-hoc group effects at specific time points. Statistical analysis will be performed using SAS software.

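### The quality-of-life models list neither the baseline score nor the randomisation factors; the primary hazard ratio intervals do not match the test level, and the Cox model is not stated to be stratified

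*Protocol article*

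**What the plan says.** All of the analysis wording is in the protocol article, section Data analysis. For every longitudinal outcome, "the explanatory model will contain both treatment group, time point of measurement and their interaction". The stated purpose is to test arms against each other at particular visits. Quality-of-life scores are analysed with linear mixed models. The Secondary endpoints section shows that these questionnaires are completed at baseline as well as at the end of treatment and at five follow-up visits up to month 24.

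For the primary endpoint (PMFS), "A stratified two-sided log-rank test will be used for the three pairwise comparisons of the primary analysis". The factors are then named: "Stratification factors are PSA doubling time (≤ 3 vs. > 3 months), number of metastases (1 versus > 1) and initial localization of metastases". Shortly after comes the estimate: "The hazard ratio (HR) will be determined with 95% confidence interval by means of a Cox proportional hazards model". The approach is carried over to mCRPC-FS, cPFS and OS.

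The test levels are set elsewhere. The Sample size section applies a Bonferroni correction, "implying a test-wise significance level of 0.0167". Under Interim analysis, for A versus B and A versus C, "both tests will be evaluated at a significance level of 0.0083"; if neither is significant then, "both arm B and C will be compared with arm A at the final analysis at a significance level of 0.0083".

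**The concern.** In a mixed model with arm, visit and their interaction, and no constraint at baseline, the estimated arm difference at a visit is, with complete data, essentially the raw difference in means at that visit. It carries whatever chance imbalance existed at baseline, and its standard error ignores how well the baseline score predicts the later one. Sparing patients' quality of life is part of the rationale for metastasis-directed therapy in the Abstract and Background, so precision lost on this outcome matters even though it is secondary.

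The other two matters concern agreement between test and estimate. A 95% interval beside a test at 0.0167 or 0.0083 can exclude 1 when the test is not significant, and a reader may take the interval as the result. If the Cox model left out factors that the log-rank test conditions on, the reported hazard ratio would also be a different quantity from the one tested.

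**Working it through.** **1. Baseline adjustment in the quality-of-life models.** The documents give no correlation r between baseline and follow-up scores. I assume 0.5, with a range of 0.4 to 0.7. The variance of an arm difference at one visit, relative to the raw difference, is 1 − r² with baseline adjustment and 2(1 − r) for change from baseline.

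| r | adjusted, 1 − r² | cut in variance | equivalent extra patients, 1/(1 − r²) − 1 | change score, 2(1 − r) |
|---|---|---|---|---|
| 0.4 | 0.84 | 16% | 19% | 1.20 |
| 0.5 | 0.75 | 25% | 33% | 1.00 |
| 0.7 | 0.51 | 49% | 96% | 0.60 |

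A simulation at r = 0.5 gave a ratio of 0.74 for adjusted against raw, in line with 0.75. The change score gains nothing at r = 0.5 and is less precise than the adjusted estimate at every r shown. Any gain from the three stratification factors is extra and cannot be sized from the documents.

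**2. Interval level against test level.** The plan's own figure comes first. Inputs from the Sample size section: medians of 21, 33 and 45 months, 5 years of accrual, at least 5 years of follow-up, 10% drop-out at 5 years, two-sided 0.0167, 80% power. I take survival and drop-out as exponential and accrual as uniform.

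- B versus C: HR = 33/45 = 0.733.
- Events (Schoenfeld) = 4(2.394 + 0.842)² / (ln 0.733)² = 436.
- Mean event probability in B and C = 0.746, so 436/(2 × 0.746) = 292.2 per arm. The stated 291 is reproduced.
- At 291 per arm, about 434 events and 79.9% power.

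From 434 events:

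- SE of log HR = 2/√434 = 0.096.
- A 95% interval excludes 1 in favour of C if HR < exp(−1.960 × 0.096) = 0.829.
- The test at 0.0167 needs HR < exp(−2.394 × 0.096) = 0.795.
- An observed HR between 0.795 and 0.829 therefore gives the two different messages.
- Chance under the planned effect: the expected z is 0.310/0.096 = 3.23, so Φ(2.394 − 3.23) − Φ(1.960 − 3.23) ≈ 0.099.
- Chance under the null, both directions: 0.05 − 0.0167 = 3.3%.

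For A versus B at the final analysis (about 493 events) the cut-offs are 0.838 for the 95% interval, 0.806 for a test at 0.0167 and 0.788 for a test at 0.0083. For A versus C (about 465 events) they are 0.834, 0.801 and 0.783. Under the planned effects the mixed result is rare for both: below 1% for A versus B and negligible for A versus C.

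Matching intervals are 98.33% at 0.0167, which are 2.394/1.960 = 1.22 times as wide on the log scale, and 99.17% at 0.0083, which are 2.640/1.960 = 1.35 times as wide.

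**3. Cox model with and without strata.** The documents give neither the prognostic strength nor the prevalence of the three factors. I assume three independent binary factors at 50% with equal hazard ratios. Each setting has 300 simulated trials of 291 per arm, true HR 0.733, arms balanced within the eight strata, and censoring as above.

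| assumed HR per factor | mean HR, unstratified | mean HR, stratified |
|---|---|---|
| 1.0 | 0.737 | 0.736 |
| 1.5 | 0.754 | 0.740 |
| 2.0 | 0.767 | 0.730 |

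The Monte Carlo standard error of each mean is about 0.733 × 0.096/√300 = 0.004.

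**The case against.** Four things can be said for the plan, and much of each stands.

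- **The Cox sentence is silent, not unstratified.** It follows directly on a stratified test and a list of strata, and a condensed article may leave the detail to the full protocol or analysis plan. A reader might infer that the strata are left out; the text does not say so. Even an unstratified Cox model would give a marginal hazard ratio rather than a wrong one, and the stratified primary test would be unaffected.
- **Baseline may already be in the model.** The text lists terms that the model will contain without saying only those, and baseline may be one of the modelled visits. So one cannot say that the models ignore baseline. But unless baseline means are constrained to be equal across arms, including baseline as a visit leaves the arm difference at a later visit essentially unadjusted.
- **Leaving out covariates does not bias a randomised comparison in a linear model.** This is correct. The loss is one of precision, on secondary outcomes.
- **A 95% interval beside a corrected test is common reporting.** The decision rule is the Bonferroni-level log-rank test. A reader might take the 9.9% as a rate of wrong decisions or as inflated type I error. It is neither: it is the chance of seeing the two results side by side. Type I error, power and sample size do not change. What remains is that the plan does not label these intervals as unadjusted.

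**Conclusion.** The point holds as a modest improvement to the analysis wording.

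Main part: the listed longitudinal terms do not include the baseline score or the randomisation factors, although arms are to be compared at single visits and baseline quality of life is available. Adding baseline cuts the variance of a quality-of-life difference by 25% at r = 0.5 (16% to 49% for r from 0.4 to 0.7). The correlations are assumptions, and the comparison is with an unconstrained model.

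Second: the 95% interval is a stated mismatch with tests at 0.0167 or 0.0083. For B versus C it gives an interval excluding 1 beside a non-significant test in about 9.9% of trials under the planned effect and 3.3% under the null. The consequence is confined to reporting.

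Third: whether the Cox model is stratified is unstated and should be made explicit. If it were unstratified, the hazard ratio would move towards 1 by an amount the documents do not allow one to fix: 0.754 against 0.740 at an assumed factor HR of 1.5, 0.767 against 0.730 at 2.0, and practically nothing if the factors are not prognostic.

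**What to change.** - **Quality-of-life models:** add the baseline score as a covariate, or keep baseline as a response with means constrained equal across arms, and add the three stratification factors. No new data are needed. The longitudinal sentence also covers toxicity, but no gain has been worked out for the proportional odds model, so this change is proposed for quality of life only.
- **Primary hazard ratios:** give the interval at the level of the test actually applied, 98.33% where it is 0.0167 and 99.17% where it is 0.0083. Keep 95% intervals beside them, labelled as unadjusted for multiplicity. The cost is intervals 1.22 or 1.35 times as wide on the log scale.
- **Cox model:** state that it uses the same strata as the log-rank test, for PMFS and for the endpoints that follow the same method.

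All three are wording changes that can be made before analysis. The sample size and the primary test stay as they are.

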#### Interim analysis

An interim analysis is planned approximately after 60 months and after including 179 patients in each arm. A that time we have at least 80% power to analyse arm A vs. arm B and arm A vs. arm C. To control the type I error, both tests will be evaluated at a significance level of 0.0083. If both tests are significant, arm A can be stopped. Otherwise, all arms will be continued. In such case, the final analysis will compare arms B and C at a significance level of 0.0167. In case of significance of either arm B or C versus arm A at interim analysis, the final analysis of the remaining comparisons will also be performed at a significance level of 0.0167. In case both comparisons at the interim analysis are non-significant, both arm B and C will be compared with arm A at the final analysis at a significance level of 0.0083.

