### Objectives

#### Primary endpoint

◦ Poly-Metastatic Free Survival (PMFS) will be determined from the last day of the first SBRT or from the day surgery was performed until the first day of poly-progression which is defined as the detection > 5 new lesions at PSMA PET-CT/MRI (± combined with MRI if needed to improve diagnostic accuracy). In case of poly-progression, pADT combined with chemotherapy [42–44], ARTA [28, 29, 31] or abiraterone-acetate [33, 34] will be considered the standard-of-care. The decision on which treatment will be offered will be taken on the multidisciplinary meeting in every case and will take into account former treatment. If recurrence occurs in ≤ 5 lesions, a new MDT is proposed if technically feasible and the patient will receive again the treatment he was allocated to at the time of initial randomisation. Patients free from poly-progression are censored at their last follow-up.

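### The interim's 179 patients per arm do not match its date of about month 60, when the sample size plan has all 291 per arm enrolled

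*Protocol article*

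**What the plan says.** The Sample size section of the protocol article states: "We suppose a 5-years of accrual and a minimum of 5 years of follow-up to determine the primary endpoint". It requires 873 patients, 291 per arm, with 10% drop-out at 5 years and a test-wise level of 0.0167. Its effect assumptions are a PMFS of about 21 months in arm A and gains of 12 months at each step: "We assume a delay of PMFS after MDT alone of approximately 21 months" and "We consider an additional median delay of PMFS of 12 months in arm B and another additional 12 months of PMFS in Arm C". The medians are therefore 21, 33 and 45 months.

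The Interim analysis section then states: "An interim analysis is planned approximately after 60 months and after including 179 patients in each arm". It claims that at that time "we have at least 80% power to analyse arm A vs. arm B and arm A vs. arm C", with both tests at 0.0083. The action attached to the look is: "If both tests are significant, arm A can be stopped". Otherwise all arms continue.

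**The concern.** The interim is fixed by a date and a number that come from different accrual schedules. A trial that enrols 291 per arm in 60 months does not have 179 per arm at month 60; it has 291. A trial with only 179 per arm at month 60 is not on the 5-year plan.

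Two things depend on this. The first is the power of the look: a team that acts on the number would look about two years before a team that acts on the date, with about half the A-B power. The second is the stopping action. Closing arm A to new patients can save patients only while arm A is still recruiting, and on the planned schedule recruitment is over at month 60.

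**Working it through.** **Inputs.** From Sample size: medians 21, 33 and 45 months; 60 months of accrual; at least 60 months of follow-up; 10% drop-out at 5 years; 291 per arm; final level 0.0167. From Interim analysis: month 60, 179 per arm, level 0.0083. Tests are two-sided (Data analysis). Assumptions of this check: exponential PMFS and drop-out, and even accrual.

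**Formulas.** Hazard l = ln2/median. Drop-out rate d = -ln(0.9)/60 = 0.00176 per month. P(event) is the mean of l/(l+d) × (1 - exp(-(l+d)t)) over the follow-up times t. Power = Φ(ln(ratio of medians) × √events / 2 - z), where z is the two-sided critical value.

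**Reproducing the plan's 291.** B versus C at month 120, follow-up 60 to 120 months, z = 2.393:
- Events: 231.2 + 203.0 = 434.1.
- Power: Φ(0.3102 × √434.1 / 2 - 2.393) = Φ(0.838) = 79.9%.

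The model therefore recovers the stated sample size.

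**Accrual.**
- Planned pace: 291/60 = 4.85 per arm a month.
- 179 per arm is reached at month 60 × 179/291 = 36.9.
- If 179 per arm are reached only at month 60, 291 takes 291/(179/60) = 97.5 months. Five years of follow-up then ends at month 157.5, not 120.

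**Events needed for A versus B.** 80% power at two-sided 0.0083 (z = 2.640) needs 4 × ((2.640 + 0.842)/ln(33/21))² = 237.3, so 238 events.

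**A-B power by reading.**

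| Reading | Follow-up (months) | Events A + B | A-B power |
|---|---|---|---|
| Month 60, all 291 per arm | 0 to 60 | 160.3 + 122.1 = 282.4 | 88% |
| 179th patient per arm, month 36.9 | 0 to 36.9 | 74.2 + 53.4 = 127.6 | 47% |
| 179 per arm reached only at month 60 | 0 to 60 | 98.6 + 75.1 = 173.7 | 63% |
| First 179 per arm on planned pace, month 60 | 23.1 to 60 | 127.1 + 99.1 = 226.2 | 78% |
| 179 per arm entered in 30 months, month 60 | 30 to 60 | 132.8 + 104.7 = 237.5 | 80% |

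For the first row: Φ(0.452 × √282.4 / 2 - 2.640) = Φ(1.158) = 87.7%. The last row is the one that returns 179 for 80% power at month 60, but it needs about 179/30 = 6.0 per arm a month. The even planned pace gives 4.85 × 30 = 145.5 by month 30.

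A-C power is lowest at month 36.9 (92.8%) and 98% or more in the other rows.

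**Places left in arm A.** With accrual on plan, 291 - 291 = 0 at month 60. The 238th A+B event is expected at month 53.9, with 53.9 × 4.85 = 261 per arm randomised, so 291 - 261 = 30 places are left.

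**The case against.** A reader might infer that the claim of at least 80% power is false. The text does not support that. The date and the number are joined by 'and'; on planned accrual the date comes later and governs, and the look then has about 88% A-B power. 179 is then a minimum that does not bind.

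The sample size text gives a duration, not a monthly pace. If accrual were front-loaded, with 179 per arm by month 30 and 291 by month 60, those 179 would give 80% at month 60. So the conflict over 179 and 80% depends on even accrual. This stands as a qualification, although the Interventions section has centres joining after the first, which makes a fast start unlikely.

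The reading with only the first 179 analysed is a near miss: 77.6%, or 79.1% without drop-out. That gap alone would not show an error. The text does not describe such a restriction, however, and it would set aside 291 - 179 = 112 enrolled patients per arm.

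A reader might also infer that stopping arm A can never have any effect. That goes too far. If accrual takes 66 months, about 265 per arm are in at month 60, A-B power is 83.7% and about 26 arm A places remain. At 72 months the figures are about 243 per arm, 79.6% and 48 places.

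Finally, because a man with a limited recurrence "the patient will receive again the treatment he was allocated to at the time of initial randomisation", a reader might fault the article for not saying what stopping means for re-treatment in arm A. That is operational detail which an article commonly leaves to the full protocol, and it is no part of this point.

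**Conclusion.** The point holds as an inconsistency between the interim's stated number and its stated date. On the 5-year plan, accrual is complete at month 60 with 291 per arm, whatever its shape; 179 per arm belongs near month 37 if accrual is even. It is not a demonstrated failure of power: the A-B claim is met at month 60 with all 291 (88%). With 179 per arm, A-B power runs from 47% to 78% on the readings with steady accrual and reaches 80% only with front-loaded entry. A-C power is adequate on every reading.

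Closing allocation to arm A at month 60 saves no patients if accrual finishes on plan, and saves some only if it runs late. The power figures rest on exponential times and even accrual, which reproduce the plan's 291. The final B-C comparison is not affected. The sponsor should correct this before any interim data are seen.

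**What to change.** Change the Interim analysis section in one of two ways.

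1. Keep month 60, replace 179 with the 291 per arm expected then, state about 88% A-B power, and describe the look as an early analysis of the comparisons with arm A. Cost: wording only, but it gives up closing allocation as an aim if accrual is on time.
2. If closing allocation is the aim, hold the look when arms A and B together have 238 PMFS events (80% A-B power at two-sided 0.0083, medians 21 and 33 months). On planned accrual this falls near month 54, with about 261 per arm randomised and about 30 arm A places left. Cost: no fixed calendar date, and A-B power of 80% instead of 88%.

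If 179 per arm by month 60 is in fact the expected pace, the Sample size section should instead state about 98 months of accrual, and the Interim analysis section about 63% A-B power.
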